## Abstract

Inflamm-aging refers to the chronic low-grade inflammation that occurs with aging and cellular senescence, and it is linked to various diseases. Understanding the markers involved in inflammation and aging, as well as their interaction with environmental factors and bodily control mechanisms, can provide crucial tools for assessing the resilience (i.e. the ability to adapt and improve) of the human body, particularly in the presence of chronic degenerative conditions or vulnerable life stages, that place the individual and the community to which he belongs in a state of potential fragility. HEBE focuses on physical exercise, along with nutritional and lifestyle recommendations, to reduce systemic inflammation and promote healthy aging. HEBE encompasses multiple research lines (LR). In the ongoing LR1 (“proof of concept”), healthy lifestyle recommendations were provided to University of Milan employees, and changes in quality of life and well-being were assessed using a specialized questionnaire. The first 100 eligible subjects, who expressed their willingness to participate, underwent a personalized physical exercise protocol based on clinical and objective assessments. Biomedical samples were collected at baseline (T0) and follow-up (T1) to establish a shared biobank and identify non-invasive biomarkers that monitor the impact of physical exercise on individual characteristics such as cardiovascular and metabolic health. Subsequently (LR2-LR10), the proof of concept findings will be expanded to include various conditions of vulnerability such as obesity, cancer, endocrine disorders, cardiovascular diseases, infertility, functional syndromes, respiratory disorders, neurodegenerative diseases, and autoimmune conditions. The research lines will leverage the expertise of the 94 participating investigators to form a collaborative network that maximizes the potential for investigation and knowledge exchange. This approach fosters a culture of health promotion and disease prevention.

ClinicalTrials.gov Identifier: NCT05815732.

## Background

Non-communicable diseases (NCDs) are the cause of premature aging and death of 41 million people each year, equivalent to 74% of all deaths globally [1], and specifically for 88% in the USA and 91% in Italy [2]. In this context, unsustainable lifestyles, often characterized by a lack of physical activity together with unsuited dietary habits, might trigger the development and progression of NCD [3]. To date, it is estimated that about 41% of Europeans (and as many as 60% of Italians) do not carry out any type of physical activity (even mild) and this increases the risk of chronic diseases [4].

Biological cellular aging has been recognized as a key factor in NCD [5]. Over the years, the progressive increase in the number of senescent cells can lead to tissue/organ dysfunction [6, 7]. Senescent cells undergo metabolic changes that lead to increased secretion of soluble factors (e.g. cytokines, chemokines, growth factors, metalloproteases, hormones) which concur to mold the microenvironment, thus affecting the composition and phenotype of the surrounding stromal cells, and promote angiogenesis and vasculogenesis processes [8, 9]. In addition, the removal of damaged cells, via recruiting phagocytes, promotes cell differentiation and proliferation for tissue renewal, regulating extracellular matrix (ECM) composition and structure [10]. Local inflammatory processes are mirrored at the systemic level, thus the secretion of pro-inflammatory molecules and activation of immune cells contribute to the generation of a chronic low-grade pro-inflammatory state known as "inflamm-aging", associated with the onset and progression of most age-related diseases [11, 12].

Counteracting inflamm-aging could be the key to ensuring healthy aging and reducing the risk of the early development of NCD. A very promising approach to impair inflamm-aging focuses on reducing the risk factors associated with NCDs by personalized lifestyle interventions. In particular, targeted physical activity can improve health, enhance the quality of life, and reduce the risk of developing NCD, resulting in both immediate and long-term health benefits [13]. Physical activity improves specific control mechanisms, such as cardiac autonomic and metabolic controls, and reduces inflammatory parameters according to specific immune responses both at the cellular and humoral levels [14–16]. In addition, extended clinical evidence shows that cardiorespiratory fitness is a stronger indicator of cardiometabolic risk factors and risk prediction than self-reported physical activity levels [17], and a powerful predictor of cardiovascular health in youth and later in life [18].

Understanding the early disease mechanisms represents the starting point for a “Medicine” that approaches the issue of environmental health in a preventive key, helping to reduce the incidence of diseases and the resulting mortality.

The ultimate goal of the HEBE project is to translate the results obtained in a clinical-pathological context and apply them in a public health context. In particular, we aim to apply the knowledge we are acquiring to counteract the negative consequences of inflammation-aging on health in a preventive setting. This would allow us to translate the observations obtained from basic and epidemiological studies to clinical practice, allowing us to identify the subjects most susceptible to a certain risk factor (e.g. obese, elderly, people with chronic pathologies, etc.), and to indicate effective prevention strategies.

## Objectives

The main objective of the HEBE study is the evaluation of the effects of the personalized intervention based on physical exercise on clinical parameters and circulating markers in the sampling population of employees of the University of Milan.

The primary endpoint will be the increase in maximal oxygen consumption (VO_2_ max) following the 6-month exercise program. The main secondary endpoint will be the evaluation of the effects of physical exercise on the control of the autonomic nervous system, considering the modification of the Autonomic Nervous System Index (ANSI) as the main variable. A further secondary endpoint will be the evaluation of the effect of physical exercise on the regulation of circulating levels of biomarkers. Additional endpoints will be the evaluation of the effect of physical exercise on the following parameters:

Body composition (Percentage of fat mass and free fat mass)Blood chemistry parameters (e.g. blood sugar, glucose, and lipid profile)Improved quality of life and perception of stress symptomsImproved quality/quantity of sleepImproved psychological well-being

Furthermore, the relationship among all the biomarkers deriving from the study will be evaluated mainly at the exploratory level.

## Methods/Design

### Design and conceptual framework

HEBE is a prospective cohort started in 2022, to evaluate the role of physical exercise in modulating the inflamm-aging by determining an impact on health and on the risk of developing NCD. The study has been registered in ClinicalTrials.gov (Identifier: NCT05815732; posted on April 18, 2023). The authors confirm that all ongoing and related trials for this intervention are registered.

The applied bottom-up approach involves the cooperation of 94 researchers in life sciences and medicine at the University of Milan, to create a synergy that holistically approaches the concept of inflamm-aging and evaluates its reduction by physical exercise, integrated by lifestyle changes.

Informed consent has been and will be obtained from all study subjects before their participation. This essential ethical principle was carefully observed throughout the recruitment and data collection phases of our study. Every participant was fully informed about the nature of the research, the procedures involved, and the potential risks and benefits. All methods employed in our study were conducted in strict accordance with the relevant guidelines and regulations. HEBE received Ethics Approval from the University of Milan Ethical Committee (approval 62/22, date 30/06/ 2022).

The overall project includes 10 Lines of Research (LR) as described:

LR1 ("proof of concept"), which is currently ongoing, proposes a lifestyle modification protocol to all University of Milan employees and will be used to evaluate the changes obtained in terms of quality of life and psychophysical well-being using questionnaires. LR1 is focused on physiological mechanisms and thus the recruitment involves only healthy subjects (accounting for cardiometabolic risk factors). We will broaden and deepen the study of biological processes at the basis of the senescence processes of the human organism, and in particular, we will define how these mechanisms change about the systemic and tissue / organ-specific inflammatory state, with physical exercise. The choice of measures that are carried out in the proof of concept, has been focused on the assumption that all levels of biological organization need to be investigated, from molecular, cellular, tissue, and organ studies, to studies that investigate model organisms as a whole (e.g., mouse model, zebrafish).

Concepts defined in LR1 will be then applied to 9 additional LRs, declining the common background of inflamm-aging and evaluating the effect of physical exercise on additional sub-cohorts according to the following lines of research (Fig 1).

**Fig 1 pone.0300011.g001:**
[figure not shown]
Conceptual framework for the HEBE research. The concepts established in Line of Research (LR) 1 (“proof of concept”) serve as the foundation for investigating nine additional LRs. These LRs focus on distinct aspects of inflamm-aging and explore the impact of physical exercise on various sub-cohorts. The planned lines of research are as follows: LR2: Obesity and Comorbidity Development; LR3: Cancer and Inflamm-Aging; LR4: Endocrine Factors in Fragility; LR5: Cardiovascular Disease in Inflamm-Aging; LR6: Inflamm-Aging and Human Fertility; LR7: Psychological Stress and Inflamm-Aging; LR8: Respiratory Diseases and Inflamm-Aging; LR9: Neuroinflammation, Aging, and Frailty; LR10: Autoimmune Diseases and Inflamm-Aging. Each line of research extends from the foundational LR1, collectively contributing to a comprehensive understanding of inflamm-aging and its diverse implications.

LR2: Obesity and development of comorbidities;LR3: Cancer;LR4: Endocrine origin of fragility;LR5: Cardiovascular diseases;LR6: Human fertility;LR7: Psychological stress;LR8: Respiratory diseases;LR9: Neuroinflammation associated with aging and frailty;LR10: Autoimmune diseases.

### Subjects enrolled in LR1—Phase 1

A lifestyle modification protocol has been proposed to all University of Milan employees, by sending an email from and to the institutional accounts. The University of Milan (“Università degli Studi di Milano”, UNIMI) is a founder and the only Italian member of the prestigious League of European Research Universities (LERU). UNIMI employees include 2605 teachers and 1872 technical and administrative staff. Those willing to adhere to the protocol have been asked to fill in at time zero (T0) a questionnaire that will investigate lifestyle habits (physical activity, sedentary lifestyle, nutrition, smoking, perception of stress, sleep, alcohol, etc.), and clinical individual characteristics (November 8, 2022, starting of the recruitment period, expected to end December 31, 2024). After answering the questionnaire questions, participants are asked to adhere as much as possible to specific recommendations in the following 6 months. Suggestions for a lifestyle change towards healthy habits are delivered to participants through texts published on the HEBE website (https://hebe.unimi.it), which has been specifically created and curated by researchers of the University of Milan with specific expertise in the topics of interest, to guarantee that all recommendations, indications, and messages delivered are based on scientific data and evidence-based medicine (EBM). Specifically, the HEBE website has been structured with a dedicated section named “live healthy”, including specific information related to physical activity, nutrition, psychophysical well-being (e.g., sleep habits, stress management, stopping smoking) and simple tools for the qualitative self-measure of health basic parameters, such as Body Mass Index, waist circumference, Healthy Diet Score, etc. This information is also provided weekly in the HEBE Social Media official Instagram profile (@hebe_unimi).

After 6 months (T1), each subject is invited to fill in again the same questionnaire, integrated with additional questions to ascertain the subjects’ compliance. This second assessment is aimed at investigating the changes obtained in terms of lifestyle, quality of life, and psychophysical well-being. So far (September 20, 2023), 983 subjects filled out the questionnaire (21.9% of the involved UNIMI personnel).

At the end of this questionnaire (T0), the subjects also have the opportunity to express their willingness to be part of a personalized medical intervention (positive answer: n = 390, see Phase 2).

### Sample size

For sample size assessment [19–22] we focused on the primary objective and the endpoint related to the variation of the measures of VO_2_ max over the observation period. Using a Student’s t-test for paired data with a level of significance α = 0.050, a sample size of 100 pairs of pre- and post-intervention data reaches 80% power to reject the null hypothesis of no change in VO_2_ max when the value of the effect size under alternative hypothesis is 0.28. The effect size is defined as d = (μ_1_ –μ_2_) / σ where σ the standard deviation of the population of pre vs post differences. According to Cohen (1988), the present effect size would be considered between low (0.2) and medium (0.5) reference values and therefore suitable for the needs of the study.

### Subjects enrolled in Phase 2

Enrolment criteria of this subgroup were: i) absence of myocardial infarction, neurodegenerative and autoimmune diseases; ii) absence of cardiac arrhythmias; iii) absence of osteo-muscular problems that prevent the execution of physical exercise; iv) not pregnant / breastfeeding; v) absence of psychiatric pathologies; vi) absence of oncological pathologies in the last 3 years treated with chemotherapy and immunotherapy). The age range of the participants who have expressed their willingness to participate to the personalized physical exercise protocol spans from 30 to 70 years. All the subjects gave their written informed consent to the study.

Among all the subjects who meet the inclusion criteria, participants will be divided according to the following grouping criteria (strata):

Stratification by age (50% <50 years; 50% ≥50 years);Stratification by sex (50% females; 50% males);Stratification by Body mass index (50% with BMI <25; 50% with BMI≥25).

Within each stratum, the final selection of the 100 volunteers is carried out based on the order of joining the study (Fig 2). These 100 volunteers are invited to a preliminary online information meeting with the investigators of the study to verify their actual intention to actively participate in all phases of the project, as described below.

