### Statistical analysis

The main outcome (variation of VO_2_ max along the observation period) will be evaluated across the population strata and in association with the demographic, biological, and clinical covariates of interest. Descriptive analyses will be implemented to assess measured individual variations, in line with the repeated measures we collect. General linear analysis of variance/covariance models for repeated measures will then be used. Sensitivity analyses will be performed on the missing values and the robustness of the statistical models about extreme observations and assumptions on the distributions of the measures. The possibility of adopting non-parametric and/or robust regression methods of analysis will be evaluated. About the secondary/exploratory objectives regarding the biological variables considered in the project, analyses will be carried out taking into account the problem of the multiple statistical tests through the False Discovery Rate approach. Furthermore, projective techniques of multivariate analysis will be used such as Principal Component Analysis (PCA) and its non-linear and robust extensions according to inductive inference approaches (computational learning) to reduce the size of the problem and extract the most relevant information also by the structure of repeated measures of the study. A final statistical analysis plan (SAP) will be prepared during the conduct of the study before performing the final analyses.

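### The 100 volunteers selected equal the 100 complete VO2max pairs that the 80% power figure needs, with no stated allowance for loss over six months

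*Protocol article*

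**What the plan says.** The Objectives section makes the increase in VO2max after the six-month exercise programme the primary endpoint. The Sample size section bases the study size on that endpoint, using a paired Student's t-test "for paired data with a level of significance α = 0.050". It says that "a sample size of 100 pairs of pre- and post-intervention data reaches 80% power to reject the null hypothesis of no change" when "the value of the effect size under alternative hypothesis is 0.28". The effect is expressed in units of the standard deviation of the pre-post differences. The section judges it suitable because it lies between Cohen's reference values of 0.2 and 0.5.

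Under Subjects enrolled in Phase 2, the article says that within strata "the final selection of the 100 volunteers is carried out based on the order of joining the study". Those selected are then invited to an online meeting "to verify their actual intention to actively participate in all phases of the project". The Abstract reports in the past tense that the first 100 eligible people went through the personalised exercise protocol.

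On incomplete data, the Statistical analysis section says "Sensitivity analyses will be performed on the missing values". The text gives no expected loss rate, no over-enrolment and no number of complete pairs expected.

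**The concern.** The power calculation counts complete pairs, whereas the selection rule counts people. The article gives both as 100, and the two agree only if essentially everyone selected provides a usable VO2max value at both time points.

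Some loss is plausible from the article's own description. The programme runs for six months and is followed at home, with attendance at a training centre optional. Contacts at least monthly are planned to help participants with difficulties (Physical exercise prescription). The endpoint comes from an incremental cycle test that must reach a respiratory quotient of at least 1.1 (Cardiopulmonary Test section), so a participant may attend the second visit and still not give a valid value. The planned sensitivity analyses for missing values acknowledge incomplete data, but they cannot restore lost pairs.

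At stake is how a null or borderline result on the primary endpoint is read. This calculation is the only justification given for the study's size. If 80% is carried forward to a smaller analysed sample, the result will be judged against more power than the study had.

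**Working it through.** **Inputs from the article.** Significance level 0.05, effect d = 0.28 in units of the SD of the differences, 100 pairs, 80% power (Sample size); 100 people selected (Subjects enrolled in Phase 2); six-month programme (Objectives). Sidedness is not stated. **Assumed here:** loss rates of 5%, 10% and 20%, because the article gives none.

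**Formula.** For n complete pairs, the paired t statistic follows a noncentral t distribution with n − 1 degrees of freedom and noncentrality d√n. Two-sided power is P(T > t₀.₉₇₅,ₙ₋₁) + P(T < −t₀.₉₇₅,ₙ₋₁). The normal approximation is Φ(d√n − 1.96).

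**Step 1: reproduce the stated figure.** With n = 100, the noncentrality is 0.28 × √100 = 2.80 and the critical value is 1.984.
- Two-sided, exact: 79.2%. Normal approximation: Φ(2.80 − 1.96) = Φ(0.84) = 80.0%.
- One-sided, exact: 87.2%.

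Only the two-sided test matches the stated 80%, so it is used below. The effect giving exactly 80% with 100 pairs is 0.2829, which rounds to the stated 0.28. The article's figure is therefore reproduced. It has no slack: at d = 0.28 the exact test first reaches 80% with 103 pairs.

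**Step 2: power when pairs are lost** (two-sided, d = 0.28).

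| Complete pairs | Loss from 100 | Noncentrality 0.28√n | Power | d detectable with 80% power |
|---|---|---|---|---|
| 100 | 0 | 2.800 | 79.2% | 0.283 |
| 98 | 2% | 2.772 | 78.4% | 0.286 |
| 97 | 3% | 2.758 | 77.9% | 0.287 |
| 95 | 5% | 2.729 | 77.1% | 0.290 |
| 90 | 10% | 2.656 | 74.8% | 0.299 |
| 80 | 20% | 2.504 | 69.6% | 0.317 |

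**Step 3: reading the table.** Losing one or two pairs makes no practical difference. From three lost pairs, power is more than two points below the stated 80%. It is about 5 points below at 10% loss (80 − 74.8 = 5.2) and about 10 points below at 20% loss (80 − 69.6 = 10.4). At 20% loss the chance of missing an effect of 0.28 is 100 − 69.6 = 30.4%, against the 20% implied by the stated power.

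**The case against.** Several objections have weight.

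- **The power sentence is conditional and correct.** A reader might infer that any loss makes the stated 80% false, or that the calculation contains an arithmetic error. The article does not support either reading. The sentence is about 100 pairs and reproduces at that number, and one or two lost pairs leave 78.8% or 78.4%. What is unsupported is the step from 100 pairs to 100 people. This objection stands in full.
- **The article's own justification survives.** It calls 0.28 suitable because it lies between 0.2 and 0.5, and does not present it as an effect expected from data. The detectable effect at 20% loss, 0.317, is still in that range. This stands, and it limits the importance of the point.
- **A rule for replacements may exist.** A reader might infer that the study has none. The figure on the Phase 2 selection process is not available in the text, an article commonly leaves such rules to the full protocol, and the Abstract suggests that 100 people had already started. The 390 who expressed willingness are counted at the end of the Phase 1 questionnaire, before the eligibility criteria and strata are applied, so the reserve in each stratum is unknown. This stands: the absence of a replacement rule is not part of the point.
- **The loss rates are assumed, and retention is addressed.** The intention check and regular contacts may limit loss, but they add no participants. This stands as a limit on the figures. It does not explain why the two numbers are equal.
- **A repeated-measures model could keep incomplete cases.** A person with only a baseline value adds little information about change, so this recovers little power.

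**Conclusion.** The point holds as a mismatch between two numbers that the article itself prints, so it is more than detail left to a fuller document. The number selected equals the number of complete pairs required, and no allowance for loss is stated although missing values are foreseen. The design therefore delivers about 80% power at d = 0.28 only if almost no one is lost.

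The size depends on the unknown loss rate: a few points of power at 5%, about 5 at 10% and about 10 at 20%. These figures assume a two-sided test, which is inferred because only that test reproduces the stated power. They also assume that loss only reduces the number of pairs and leaves the effect and the SD of the differences unchanged.

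The point is moderate. The type I error and the definition of the endpoint are unaffected, and the study remains able to detect an effect between the small and medium benchmarks.

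**What to change.** State in the Sample size section, or in the final SAP that is still to be prepared before the final analyses, how many complete pre/post pairs are expected from the 100 people selected. Then restate the power or the detectable effect for that number, and say that the test is two-sided if that is what was used. For example: *100 selected; about 80 to 90 complete pairs expected; 80% power for d of about 0.30 to 0.32, or about 70% to 75% power for d = 0.28 (two-sided, alpha 0.05).* The range of 80 to 90 is a placeholder for the investigators' own expectation.

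The cost is a sentence or two and a slightly less favourable figure. No further recruitment is needed, and no replacement rule is asked for, since intake may already be complete.
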